## Methods

### Overall design and timeline

The current study will employ a multi-site, longitudinal, blinded randomized controlled trial (RCT) design with a target sample of 120 older adults without dementia or MCI (see inclusion criteria below). Sixty older adults completing TAPAT will be compared to sixty older adults completing the active control condition (computer-based games; see Fig. 1). Total participation time is approximately 6 months and includes 5 in-person assessment sessions. Assessments will be performed at University of Iowa (Iowa City, IA) and VA Boston Healthcare System (Boston, MA). The first assessment session (V0) involves screening for eligibility (see inclusion/exclusion below). If the participant is eligible, baseline assessments are administered in a second visit (V1) to characterize their cognitive and functional abilities before training. After the baseline assessment, older adults are randomized to either the TAPAT or control training program and complete approximately 12–16 weeks of in-home training, while monitored and coached by a research assistant (*cognitive remediation coach*). Participants assigned to the experimental software treatment program will be randomly assigned to receive performance feedback (version A.1 vs. A.2) in the first or the second half of training. Participants will then be asked to complete a mid-training assessment (V1.5) and will be administered a subset of assessments comprised of the secondary outcome: mindfulness. At the mid-training assessment, participants who were randomized to the experimental program will switch program versions (i.e., participants that trained on version A.1 will begin version A.2, and vice versa), such that participants train on both versions. To measure potential training-related improvements, participants will be assessed immediately after the completion of the total training (V2) by an assessor that is blind to group affiliation. To measure the persistence of potential training-related improvements, participants are also assessed after a three-month no-contact period (V3), again by an assessor blind to group affiliation. After this visit, participant activities are completed and trial participation ends.

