#### Blinded site roles

All site staff responsible for the administration and scoring of participant assessments will remain blinded to participant treatment. Site Principal Investigators will be required to complete a Delegation of Authority Form prior to the start of the study, indicating which activities individual site research team members will be authorized to complete. Site Principal Investigators will also remain blinded.

To prevent un-blinding, the following controls will occur at the site level:The treatment condition and the control condition will be identified as “Treatment A” and “Treatment B”;Participants will be reminded not to discuss details related to treatment with psychometricians and/or clinical evaluators during the informed consent process as well as prior to initiation, and at the conclusion of, each assessment visit;Site personnel will be instructed to not discuss details of either treatment arm during open participant groups or forums;Sites will be required execute the protocol in a manner that minimizes the possibility of accidental un-blinding of psychometricians or clinical evaluators (e.g. unintended viewing of treatment sessions);Sites will be asked to post signage in appropriate areas throughout the facility reminding staff and participants to not discuss treatment details in open locations.

At the half-way point of the trial, and at the end of the trial, psychometricians will be asked questions designed to evaluate the integrity of the blinding procedures employed throughout the study.

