### Foreseeable risks, Risk Management & Emergency Response

Participation in the study presents minimal risk. The probability and magnitude of harm or discomfort anticipated in this research study are not greater than those ordinarily encountered in daily life or during the performance of routine physical or psychological examinations or tests. Study participation may be discontinued when a participant voluntarily withdraws from the study (e.g. due to scheduling issues or changing residence) or when they express discomfort with any of the study procedures (e.g. excessive frustration, boredom, or eye strain). To improve adherence to the interventions, weekly check-ins were performed to monitor participants’ progress, motivate and provide feedback, and allow participants to voice any adverse effects.

Serious adverse effects from prior studies of the treatments under study have not been reported. The protocol details potential risks related to study participation and includes assessments of depression and suicidality at baseline, week 13, and week 26 (end-of-study). Participants will be encouraged to report any adverse effects occurring during the duration of the study to the point of contact within research staff. PSC does not provide compensation for research-related injuries and will not reimburse or pay medical expenses for the treatment of research-related injuries.

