We will conservatively follow guidelines for medical devices in the reporting of adverse events in this trial, which defines unanticipated adverse device effects (UADEs) in The Code of Federal Regulations in 21 CFR 812.3(s) as any serious adverse effect on health or safety of any life-threatening problem or death caused by, or associated with, a device, if that effect, problem, or death, was not previously defined in nature, severity or degree of incidence in the investigational plan or application (or supplementary plan or application). Furthermore, an effect is classified as an UADE if it is judged by the Site PI to be a serious problem associated with a device that related to the rights, safety, or welfare of participants. We will operationalize this definition of a serious problem as one that results in any of the following outcomes: death, life-threatening situation, inpatient hospitalization atypical of the participant’s diseases condition, persistent or significant disability/incapacity; or any other adverse event that, based upon appropriate medical judgment, may jeopardize the participant’s health or the health and well-being of all participants enrolled in the study.

Site Study Coordinators, Psychometricians, and Cognitive Remediation Coaches will ask about any UADEs during each contact with participants and will be alert to any volunteered UADEs. All UADEs will be documented on a standardized eCRF and will be classified by the blinded Site PI to their degree of seriousness and their relationship to the study software.

All UADEs, whether or not we believe them to be related to the protocol, will be reported to the Site IRB according to the investigational site’s IRB procedures and to Study PI ([name]) as soon as possible, but in all cases within 10 working days of the event. PSC will circulate UADE reports to the Research Monitor and all trial sites within 10 working days of receipt. Each study site will report immediately to: 1) University of Iowa IRB, 2) PSC IRB, or 3) At the Boston VA, UADEs will be reported to the VA Central IRB electronically through a secure SharePoint system and confirmed by phone to [name].

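### Blinded psychometricians must ask about device effects at each contact, which opens an avoidable route to unblinding; the A/B masking labels also look decodable

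*Protocol article*

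**What the plan says.** Under Blinded site roles, the article states that "All site staff responsible for the administration and scoring of participant assessments will remain blinded to participant treatment". Among the controls against unblinding it lists: "Participants will be reminded not to discuss details related to treatment with psychometricians and/or clinical evaluators". The reminder is given at consent and again before and after each assessment visit. Sites must also run the protocol so that accidental unblinding of psychometricians is kept to a minimum. Psychometricians are questioned about the integrity of the blind halfway through the trial and at its end.

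Under Foreseeable risks, Risk Management & Emergency Response, the article states that "Site Study Coordinators, Psychometricians, and Cognitive Remediation Coaches will ask about any UADEs during each contact with participants"; the same staff are to be alert to events that participants volunteer. The underlying definition is narrow: "any serious adverse effect on health or safety of any life-threatening problem or death caused by, or associated with, a device". Reported UADEs "will be classified by the blinded Site PI to their degree of seriousness and their relationship to the study software".

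On labels, Blinded site roles says: "The treatment condition and the control condition will be identified as" Treatment A and Treatment B. Overall design and timeline says that participants in the experimental arm are "randomly assigned to receive performance feedback (version A.1 vs. A.2"), and the treatment description and Table 1 use the same version names.

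**The concern.** At one visit, a participant is told not to discuss treatment with the psychometrician and is then asked by that psychometrician about effects of the study software. A participant who answers by describing what was on the screen could reveal the arm. The listener is the person whose blinding protects the assessor-administered part of the primary outcome.

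The labels raise a related worry. If Treatment A is the arm whose versions are A.1 and A.2, an assessor who learns a participant's letter can infer the arm. Because the labels are fixed for the whole trial, the same inference then holds for every participant whose letter is known.

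**Working it through.** No arithmetic settles this; the check sets the sections side by side.

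1. **Are the people who ask the people who are blinded?** Yes. Psychometricians are named in the list of staff who ask about UADEs. Staff who administer and score assessments are declared blinded, and psychometricians are named there as the people to be protected from unblinding.

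2. **Can both instructions be obeyed?** Yes. The reminder covers details of treatment. The question covers serious events: death, a life-threatening situation, atypical hospitalisation, lasting disability, or another event that medically jeopardises health. A hospital stay can be reported without a word about the program. The psychometrician need not probe causality, since the blinded Site PI judges it.

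3. **Is there still a route to disclosure?** Yes. The narrow definition limits which events count, not what a participant says in reply. Participants are not expected to classify events first. The same section names frustration, boredom and eye strain as discomforts with study procedures, and a remark on any of these could describe the program. The arms are easily told apart: a continuous performance task against six commercial computer games. The article gives no rule for putting the question without inviting such remarks.

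4. **Which contacts matter?** V0 and V1 come before randomisation, so there is nothing to disclose. V1.5, V2 and V3 remain. A disclosure at V1.5 could reach the primary V2 scoring, and one at V2 could reach V3, if the same psychometrician returns. The article does not say whether that happens. A question put at V2 before the battery could affect V2 directly.

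5. **How much of the primary composite is exposed?** The composite averages six tests. From their descriptions, Attentional Blink and Category Switch appear to be computer-run. That leaves 6 − 2 = 4 that appear to be assessor-administered: Trails B, verbal fluency switching, Auditory Consonant Trigrams and Digit Span backward. The article does not state the mode of scoring outright, so this split is an inference.

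6. **Who else could ask?** Coaches are unblinded and separate from assessment staff. Weekly check-ins let participants voice adverse effects, and participants also have a contact in the research staff. Coordinators are already on the list of those who ask, but the article does not say whether they are blinded. Un-blinded site roles names only coaches and the sub-investigators who register participants, and those sub-investigators may take no part in follow-up. V3 comes after three months without contact, so someone who does not score outcomes has to be assigned to ask there.

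7. **Are the labels decodable?** The shared letter suggests that Treatment A is TAPAT, but no section says so. Nor does any section say that assessors see a participant's letter.

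8. **Can the bias be sized?** Its size would depend on the share of participants whose arm is disclosed, the resulting shift in scoring, and the share of the composite exposed to it. The article gives no figure for the first two, and only the inference in step 5 for the third. No numerical estimate is justified.

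**The case against.** The strongest reply is that the question concerns serious events only, and such events should be rare. The article notes: "Serious adverse effects from prior studies of the treatments under study have not been reported". Reminders bracket every assessment visit, sites carry a general duty to avoid unblinding, and the halfway check allows correction for later assessments. The wording and timing of the question are operational details that a condensed article may leave to the full protocol or an assessor manual. V3 may also be one of few chances to elicit events after training, so removing a questioner has a safety cost.

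Most of this stands, and it limits the size of the problem. It does not remove the point. That psychometricians ask at each contact is a stated rule, not an omitted detail. The general duty to avoid unblinding sits awkwardly beside a mandated question. A halfway check can prompt correction later but cannot undo scores already given.

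A reader might infer more than the text supports:
- **That the two sections flatly contradict each other.** They do not, by step 2 of the working.
- **That any resulting bias must favour TAPAT.** That assumes a direction of assessor preference which nothing in the article establishes.
- **That nothing is gained by having assessors ask.** The V3 visit shows otherwise.
- **That the blind is already broken by the labels.** That would need an assessor to learn a participant's letter, which the article does not describe.

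**Conclusion.** The point holds in a limited form and is a cheap improvement. A stated procedure has blinded outcome assessors put a question whose answer could reveal the arm, at visits that include V1.5 before the primary assessment. The route is avoidable. Its size cannot be derived from the documents and is probably small, because the question targets serious events, reminders are in place, and two of the six primary components appear to be computer-run.

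The conclusion rests on three assumptions: that some participants would describe the program when asked, that assessors may meet the same participant again or ask before testing, and that four components are assessor-administered. The label point is conditional on an assessor learning a participant's letter and on Treatment A being TAPAT, as the version names suggest.

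**What to change.** Reconcile the two sections so that staff who do not assess outcomes ask about UADEs: coaches during training, and a coordinator or other named non-assessor at V3. State that this person does not administer or score assessments. Psychometricians continue to record events that participants volunteer.

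Where a psychometrician must ask, the question should come only after the battery has been administered and scored, from a script that does not refer to the program. This is the weaker option, because a disclosure at one visit can still carry over to the next.

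Replace the masking labels with ones that do not share the letter of the TAPAT version names; participant-level codes would also stop one disclosure from decoding others.

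The cost is a wording change in the two sections and new labels, with no effect on sample size or analysis. The downside is one fewer routine occasion for eliciting events, which is why the non-assessor contact at V3 has to be written in.

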### Data management

We will take all standard and appropriate steps to protect the privacy and confidentiality of participants in this trial. All data collected in this study (with one small exception for electronic usage data captured directly from program use, discussed below) will be from clinician- or psychometrician-administered structured interviews, neuropsychological or functional assessments. Following consent, each participant will be assigned a standardized Participant Identification Number (PIDN). All study-related data will be recorded into a secure, web-based electronic case report form (eCRF) at each site. This system meets all relevant privacy and security standards for electronic clinical trial data entry and storage, as well as the Health Insurance Portability and Accountability Act (HIPAA) standards for confidentiality and privacy. All eCRF data entry will use the only PIDN and not the participant name, Each site will transcribe and upload de-identified data and de-identified source documentation into the study database for the purpose of data monitoring.

To help meet the highest standard of clinical trial management, a Data Safety Monitoring Board (DSMB) independent of the Sponsor and/or study Principal Investigator(s) was established to provide independent overview of safety data, aggregate study data, data management processes, and a priori analyses of primary and secondary endpoints. A DSMB Chairperson shall be appointed in advance to document member attendance and study outcomes (including the statistical methods employed to complete analyses).

### Data analysis

The data analysis plan a priori defines a primary intent-to-treat (ITT) population, a set of secondary evaluation populations, a primary outcome measure, a set of secondary outcome measures, a single primary evaluation time point, a secondary evaluation time point, a primary statistical analysis methodology, a criterion for statistical significance, and guidance for interpretation of results. There will be no interim analyses.

The primary ITT population is defined as all participants who complete a set-up (V1) visit. Note that this includes all randomized participants except those who drop/withdraw post-randomization and pre-setup visit. In total, there are three a priori defined analysis populations, including a primary analysis population (i), a secondary analysis populations designed to compare effect sizes in populations with no missing data (ii) and a tertiary analysis population who completed all training visits (iii)i.*Intent to Treat (ITT) population:* This is the a priori primary analysis population, defined as including all randomized participants who completed a V1.ii.*Intent to Treat (ITT) Fully-Evaluable (FE) population:* This is a secondary analysis population, defined as including all members of the ITT population that complete a V2 visit (the ITT-FEV2 population), or all members of the ITT population that completed a V3 visit (the ITT-FEV3 population). Note that a participant may complete a specific visit but have missing data for a test in which case the participants is in the overall FE population but does not contribute data to the FE population for that visit, e.g., the number of evaluable cases for a specific test on a specific visit may be smaller than the FE population for that visit because of missing data.iii.*Intent to Treat (ITT) Fully-Trained (FT) population:* This is a secondary analysis population, defined as including all members of the ITT-FE population who complete a target number of training visits (65 visits). Note that the FT populations are strict subsets of the FE populations; a person who completes the target number of training visits but does not complete the evaluation visit is not a member of the FT population.

The primary executive function outcome measure is a composite measure composed of the main neuropsychological assessments, specifically includingTrails B (raw score) – Trails A (raw score)DKEFS verbal fluency (switching raw score)Auditory Consonant Trigrams (sum of 9 s, 18 s and 32 s delay raw scores)WAIS Digit Span (backward raw score)Attentional Blink task (second target accuracy, raw score)Category Switch task (incongruent – congruent trials reaction time)

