### Repeated assessment battery

Once a participant is deemed eligible for participation based on their V0 results, they are next scheduled for their baseline session on the repeated assessment battery (V1), which takes approximately two hours. After completing this baseline assessment, participants are randomly assigned to either experimental or control training conditions (see below). Then, following the program set-up visit and after completing the first half of the training sessions, they will be administered an abbreviated mid-training assessment (V1.5) comprised of mindfulness-related measures. Immediately after total training is completed, participants are re-administered the baseline assessment battery (V2) and again after a three-month no contact period (V3).

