### Randomization

Participants will be randomized after the baseline visit and before the planned first day of program use. All V0 and V1 data for each participant must be fully monitored, with all queries resolved, before randomization may take place. We will use a randomization server (sealedenvelope.com) that implements the random permuted blocks within strata procedure [49, 50] with strata as age (*Older Adults 65–74* or *Older Adults* ≥ 75 years of age), allocation ratio is 1:1. Participants who are randomized to the experimental treatment group will also be randomized to either receive version 1 (experimental treatment with performance feedback) or version 2 (experimental treatment without performance feedback); at the mid-training assessment, participants will undergo a reversal of the version type such that all participants completing the entirety of the training will have trained on both versions of the experimental training program. The Site Coordinating Center will issue a randomization assignment at the appropriate time. This approach represents a best practice approach to randomization, implementing an automated centralized group assignment procedure with allocation concealment, and effective separation of sequence generation and allocation concealment.

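### The population called ITT leaves out participants lost between randomisation and program set-up, and the label set-up (V1) merges two different visits

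*Protocol article*

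**What the plan says.** Data analysis defines the primary population twice. The lead sentence reads: "The primary ITT population is defined as all participants who complete a set-up (V1) visit". A note then spells out the consequence: "this includes all randomized participants except those who drop/withdraw post-randomization and pre-setup visit". A few lines later, item (i) of the list of populations gives the ITT set as "defined as including all randomized participants who completed a V1".

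The rest of the article fixes what V1 is and when it happens. Overall design and timeline makes V1 the second visit, at which the baseline assessments are given. Repeated assessment battery says: "After completing this baseline assessment, participants are randomly assigned to either experimental or control training conditions". Randomization requires: "All V0 and V1 data for each participant must be fully monitored, with all queries resolved, before randomization may take place". It also says: "Participants will be randomized after the baseline visit and before the planned first day of program use". Repeated assessment battery mentions the program set-up visit separately, after random assignment and before the mid-training assessment.

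**The concern.** An intention-to-treat set is fixed by randomisation alone. Here membership of the set called ITT also depends on attending a visit that comes after assignment. That is a modified ITT set, whatever its name.

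The visit label adds a second problem. In the lead sentence V1 stands for set-up. In every other section it stands for baseline. A reader who applies the article's own V1 to item (i) gets all randomised participants. A reader who follows the lead sentence and its note gets a smaller set. An analyst could cite the article for either.

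The choice matters beyond the name. The article screens baseline variables for group differences in the ITT population and enters any with p < 0.1 as covariates in the mixed model. Participants with only baseline data count fully in that screen, so who belongs to the set can change the covariates of the primary model. The fully-evaluable and fully-trained sets are defined as subsets of ITT and inherit the wording. Their membership would hardly change, because they also require a completed V2 or V3 visit.

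**Working it through.** **Step 1: order of events.** From Overall design and timeline, Repeated assessment battery and Randomization:

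V0 screening → V1 baseline → V0 and V1 queries resolved → randomisation → program set-up → training → V1.5 → V2 → V3.

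V1 comes before randomisation and set-up after it, so one label cannot serve both.

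**Step 2: the sets that result.** Let x be the share of randomised participants lost between randomisation and set-up.

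| Text | Meaning given to V1 | Resulting set |
|---|---|---|
| Lead sentence with its note | set-up | 100% − x of those randomised |
| Item (i) | baseline, as elsewhere | 100% of those randomised |
| Item (i) | set-up, as in the lead sentence | 100% − x of those randomised |

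The first two rows agree only if x = 0. On the third reading the two texts agree, but the set is still defined by a post-randomisation event.

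**Step 3: how many people.** The article does not give x. One person is 1/120 = 0.8%. For an assumed x of 2% to 5%, the number is 0.02 × 120 = 2.4 to 0.05 × 120 = 6.

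**Step 4: effect on the primary estimate.** Those excluded have complete V1 data, and the planned analysis handles missing data by maximum likelihood, so they can be kept. Suppose they have no V2 data. If D is the change in an arm's baseline mean from adding them, and b is the slope of post-training score on baseline score, the arm's estimated mean change moves by b × D − D = (b − 1) × D.

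Assume a loss from one arm only, with those lost 0.5 baseline SD below the rest, and b = 0.7. The shift in the group-by-time estimate is then:

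- 2% lost: D = −0.01, shift = 0.3 × 0.01 = 0.003 SD
- 5% lost: D = −0.025, shift = 0.3 × 0.025 = 0.0075 SD
- 10% lost: D = −0.05, shift = 0.3 × 0.05 = 0.015 SD

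For scale, the example under Strengths uses a between-group difference of 5.8 − 1.0 = 4.8 points and equates 10 points with two thirds of an SD, so one SD is 15 points. The 5% case is then 0.0075 × 15 = 0.11 points against 4.8.

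**The case against.** The strongest reply is that there is only one definition. Both sentences stand in the same section and both say V1. The lead sentence equates V1 with set-up, the note explains the result, and item (i) can be read as repeating it. The exclusion is also disclosed and fixed in advance. Much of this stands. The note leaves little doubt about what was intended, and a flat claim that the article sets two rival populations against each other would go too far. The reply does not rescue the label, which has that meaning nowhere else in the article. Nor does it make the set ITT.

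A reader might also infer that the exclusion biases the trial because people leave for reasons that differ by arm. The article does not support that. It describes no arm-related reason for leaving in this interval. It labels the conditions Treatment A and Treatment B at the sites and designs the control so that participants stay blind. Coaches are unblinded, so a route exists, but its use is conjecture. The article also does not say that participants first meet their program at set-up. If they did, those who left earlier could not have been reacting to it.

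Finally, it can be said that keeping these participants gains little. For the estimate itself, that is right.

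**Conclusion.** The point holds as a defect of definition. The label set-up (V1) is wrong by the article's own account of V1, and the lead definition describes a modified ITT population under the name ITT. Item (i), read with V1 as baseline, means everyone randomised.

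The numerical effect is probably small: under the assumptions shown, 0.003 to 0.015 baseline SD for a one-sided loss of 2% to 10%. This rests on assumed loss rates, an assumed 0.5 SD baseline difference and b = 0.7. It also assumes that those excluded have baseline data only and that the model links each participant's repeated scores. Without that link b is effectively 0, and the shift at 5% is 0.025 SD.

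Two further inferences are not supported. Restoring these participants would not systematically dilute the effect, because a likelihood analysis does not assign zero gain to someone without V2. It would also not recover outcomes that were never measured. What is gained is a primary set that preserves randomisation, can be read in only one way, and fixes the sample for the covariate screen.

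**What to change.** In Data analysis, and in the analysis plan if it repeats the wording:

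- Define the primary ITT population as all randomised participants, analysed in the arm to which they were assigned.
- Delete the exclusion of those who withdraw between randomisation and set-up.
- Delete the label set-up (V1), keep V1 for the baseline visit only, and give the set-up visit its own name.
- If a set that requires set-up is wanted, name it modified ITT and use it only for a sensitivity analysis.
- Report by arm how many participants were lost between randomisation and set-up.

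The cost is a change of wording and trivial analysis work. No new data are needed, since every randomised participant has V1 data by design.
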